## Abstract

**Introduction:**

Multidisciplinary team meetings (MDMs), also known as tumor conferences, are a cornerstone of cancer treatments. However, barriers such as incomplete patient information or logistical challenges can postpone tumor board decisions and delay patient treatment, potentially affecting clinical outcomes. Therapeutic Assistance and Decision algorithms for hepatobiliary tumor Boards (ADBoard) aims to reduce this delay by providing automated data extraction and high-quality, evidence-based treatment recommendations.

**Methods and analysis:**

With the help of natural language processing, relevant patient information will be automatically extracted from electronic medical records and used to complete a classic tumor conference protocol. A machine learning model is trained on retrospective MDM data and clinical guidelines to recommend treatment options for patients in our inclusion criteria. Study participants will be randomized to either MDM with ADBoard (Arm A: MDM-AB) or conventional MDM (Arm B: MDM-C). The concordance of recommendations of both groups will be compared using interrater reliability. We hypothesize that the therapy recommendations of ADBoard would be in high agreement with those of the MDM-C, with a Cohen’s kappa value of ≥ 0.75. Furthermore, our secondary hypotheses state that the completeness of patient information presented in MDM is higher when using ADBoard than without, and the explainability of tumor board protocols in MDM-AB is higher compared to MDM-C as measured by the System Causability Scale.

**Discussion:**

The implementation of ADBoard aims to improve the quality and completeness of the data required for MDM decision-making and to propose therapeutic recommendations that consider current medical evidence and guidelines in a transparent and reproducible manner.

**Ethics and dissemination:**

The project was approved by the Ethics Committee of the Charité – Universitätsmedizin Berlin.

**Registration details:**

The study was registered on ClinicalTrials.gov (trial identifying number: NCT05681949; https://clinicaltrials.gov/study/NCT05681949) on 12 January 2023.

**Supplementary Information:**

The online version contains supplementary material available at 10.1186/s13063-023-07610-8.

## World Health Organization Trial Registration Data Set

**Table Taba:** 

Data category	Information
Primary registry and trial identifying number	ClinicalTrials.gov (NCT05681949) https://clinicaltrials.gov/study/NCT05681949
Date of registration in primary registry	12 January 2023
Source of monetary or material support	Federal Joint Committee of Germany (*Gemeinsamer Bundesausschuss; Innovationsfonds*) grant number 01VSF21047
Primary sponsor	Charité-Universitätsmedizin Berlin
Contact for public queries	[name], Department of Surgery, Campus Charité Mitte and Campus Virchow-Klinikum, Charité – Universitätsmedizin Berlin, [name]. Email: [contact]; Phone: [name]; Fax: [name]
Contact for scientific queries	[name], Department of Surgery, Campus Charité Mitte and Campus Virchow-Klinikum, Charité – Universitätsmedizin Berlin, [name]. Email: [contact]; Phone: [name]; Fax: [name]
Public title	Therapeutic Assistance and Decision Algorithms for Hepatobiliary Tumor Boards
Scientific title	Evaluation of the Trustworthiness of the Application of Artificial Intelligence and Decision Support Systems for the Creation of Tumor Conference Protocols
Country of recruitment	Germany
Health conditions or problems studied	Primary and secondary liver tumors
Interventions	No interventions
Key inclusion and exclusion criteria	Inclusion criteria are (1) patients above 18 years of age; (2) valid informed consent; (3) patient information available in the hospital information system and Health Data Platform; (4) registration in the hepatobiliary MDM; (5) diagnosis of any of the following: (a) HCC, mixed cell carcinoma, or fibrolamellar carcinoma; (b) perihilar cholangiocarcinoma; (c) intrahepatic cholangiocarcinoma; (d) colorectal liver metastases; (e) gallbladder carcinoma. Exclusion criteria are (1) patient does not consent or is incapable of giving consent; (2) patient data is unavailable in the hospital information system; (3) patient is seeking for a second opinion and not being treated at the study institution.
Study type	Monocentric, prospective, parallel randomized control trial with a non-inferiority design
Date of first enrollment	Not yet recruiting
Target sample size	1200
Recruitment status	Not yet recruiting
Primary outcomes	Concordance of recommendations of MDM-C and MDM-AB; interrater reliability of the agreement between recommendations of ADBoard and MDM-C; reproducibility of the therapy recommendations made by ADBoard
Key secondary outcomes	Completeness of decision-relevant parameters MDM protocol; explainability of ADBoard measured using the System Causability Scale (SCS) [1]

### Protocol version

Protocol version 2, dated 25 August 2023.

## Introduction

Multidisciplinary team meetings (MDMs) are a crucial component of cancer treatment [2]. MDMs are hosted regularly, usually weekly, and attended by members from various specialties, including oncologists, surgeons, radiation therapists, pathologists, and radiologists. With their combined expertise, they review patients’ medical history and examination findings, and determine the most suitable treatment plan by consensus.

Globally, primary liver cancer is the fourth leading cause of cancer-related death, with nearly 841,000 new cases and 782,000 deaths annually [3]. Demographic changes have led to an increase in older patients with hepatocellular carcinoma (HCC). The European clinical guidelines for the management of HCC strongly recommend discussion at an MDM before determining treatment interventions [3]. A multidisciplinary approach to caring for HCC has been shown to improve patient outcomes [4]. However, there are several barriers to truly effective MDMs, such as the failure of clinicians to submit adequate information in time for the MDM, physicians’ lack of personal knowledge of the patient being discussed, and time and workload pressures [5, 6].

Having a complete set of patient information at the time of the MDM is indispensable for effective decision-making [5, 6]. In the current state, simple online forms or “tumor protocols” such as the Gießen Tumor Documentation System (GTDS) [7] in Germany are used by residents to manually collect relevant patient information and parameters in preparation for the MDM. However, due to heavy clinical workloads, residents are often unable to fill out the form completely prior to the MDM. Finding information in the hospital information system and determining its relevance is time-consuming, especially for inexperienced residents. They often encounter logistical challenges in retrieving patient information [8]; for example, missing medical reports, insufficient patient history, and lack of relevant details on referral forms. Without all the necessary data, treatment decisions are either made on incomplete data or have to be postponed; consequently, the affected patients suffer delays in treatment [5, 9]. Therefore, there is potential for MDM processes to be improved, which can in turn have a significant impact on treatment decision-making and patient outcomes.

ADBoard (Therapeutic Assistance and Decision algorithms for hepatobiliary tumor Boards) aims to improve the MDM process for patients with liver cancer by using different artificial intelligence (AI) methods from the fields of natural language processing (NLP) and machine learning (ML). First, clinical text documents will be processed to automatically complete all required patient information in a conventional tumor protocol. Next, an ML model trained on MDM data will make therapeutic recommendations for specific clinical cases. The algorithm is intended for physician use only: to relieve their administrative workload of manual information collection and documentation, and to provide therapeutic recommendations.

The primary objective of this study is to assess the concordance of conventional MDM (Arm B: MDM-C) recommendations with ADBoard-supported MDM (Arm A: MDM-AB) recommendations. The reproducibility of ADBoard recommendations will be tested. The secondary objectives are (1) to examine whether ADBoard will have and use a more complete set of oncological and patient-specific parameters than is presented at MDM-C and (2) to compare the explainability of MDM-AB recommendations against that of MDM-C.

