#### Secondary outcome measures

The first secondary outcome measure is the completeness of decision-relevant parameters. To prefill the required parameters in the online tumor protocol, ADBoard searches the health information system for each required parameter. The three possible documentation statuses are (1) “present”—search performed and data are present, (2) “detected as missing”—search performed and data are absent, and (3) “missing”—search was not performed for the required parameter. The outcome is achieved if documentation is complete, defined as documentation status “present” or “detected as missing,” in ≥ 75% of all ADBoard-assisted decisions.

The second secondary outcome measure is the explainability of ADBoard measured using the System Causability Scale (SCS) [1]. The SCS consists of 10 questions. An overall score between 0.2 (lowest quality) and 1.0 (highest quality) can be achieved. Three specialist physicians at the departments of surgery and oncology will complete it, and the mean will be calculated. Achieving a mean score of ≥ 0.8 is considered to have met this outcome.

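### Explainability is promised as a comparison of MDM-AB with MDM-C, but the outcome and its success rule score ADBoard alone, so they do not test the stated hypothesis

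*Protocol article*

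**What the plan says.** All references are to the protocol article.

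- **Abstract, Methods and analysis.** A secondary hypothesis, with a direction: "the explainability of tumor board protocols in MDM-AB is higher compared to MDM-C as measured by the System Causability Scale".
- **Introduction, objectives.** Secondary objective 2 is "to compare the explainability of MDM-AB recommendations against that of MDM-C".
- **World Health Organization Trial Registration Data Set.** The key secondary outcome reads "explainability of ADBoard measured using the System Causability Scale (SCS"; MDM-C does not appear in it.
- **Secondary outcome measures.** "The second secondary outcome measure is the explainability of ADBoard measured using the System Causability Scale (SCS". On the scale: "An overall score between 0.2 (lowest quality) and 1.0 (highest quality) can be achieved". On the raters: "Three specialist physicians at the departments of surgery and oncology will complete it, and the mean will be calculated". On success: "Achieving a mean score of ≥ 0.8 is considered to have met this outcome".
- **Planned analysis.** It covers agreement, reproducibility and the completeness of parameters. Completeness is compared across the ADBoard protocol, MDM-C and the reference MDM with a Mann–Whitney U test. Explainability is not mentioned.

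**The concern.** The hypothesis and the objective are relative: one source of recommendations is to be more explainable than the other. The outcome and its success rule are absolute: one source is to reach a fixed mark. A relative claim needs a score for both sources and a contrast between them, and the outcome definition supplies neither.

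At stake is whether the second secondary objective is answered. If the plan is followed as written, the result will say whether ADBoard reached 0.8. It will not say whether ADBoard-supported protocols are easier to understand and justify than conventional ones, which is what the abstract tells readers to expect.

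**Working it through.** **1. Is there a figure to reproduce?** No. The 0.8 mark is a fixed target without a stated derivation. The sample size section is built on kappa alone and gives no effect size, SD or power for explainability.

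**2. Hypothesis and outcome side by side.**

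| | Abstract and objective 2 | Outcome section and registration table |
|---|---|---|
| Scored | MDM-AB and MDM-C | ADBoard |
| Quantity of interest | difference, MDM-AB minus MDM-C | level for ADBoard |
| Claim or rule | difference > 0 | mean ≥ 0.8 |
| Comparator | MDM-C | none |

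The other secondary outcome shows the contrast. Completeness also has a fixed threshold in the outcome section, but the planned analysis adds a comparison with MDM-C. For explainability no such step follows.

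**3. Can rule and hypothesis disagree?** Let A be the ADBoard mean and C the mean that MDM-C would obtain. The rule is A ≥ 0.8; the hypothesis is A > C. With scores chosen only for illustration, all inside the 0.2 to 1.0 range:

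- A = 0.82, C = 0.88: the rule is met (0.82 ≥ 0.8) and the hypothesis is false (0.82 < 0.88).
- A = 0.78, C = 0.60: the rule is missed (0.78 < 0.8) and the hypothesis is true (0.78 > 0.60).

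Since C does not enter the rule, the rule carries no information on the direction of the difference.

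**4. Would one added MDM-C score per physician be enough?** Assume that each of the three physicians gives one overall score per source.

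- Paired sign or Wilcoxon test: the smallest exact two-sided p is 2/2³ = 0.25 (one-sided 1/2³ = 0.125).
- Mann–Whitney test, 3 against 3: the smallest exact two-sided p is 2/C(6,3) = 2/20 = 0.10 (one-sided 1/20 = 0.05).

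None is below 0.05. A comparison therefore needs scores at case level.

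**5. Subordinate: precision of the three-rater mean.** The documents give no between-rater SD and do not state how many cases each physician scores. Assume one score per physician, SD 0.10 (range 0.05 to 0.15), and physicians regarded as a sample of possible raters. The 95% half-width is t(0.975; 2 df) × SD/√3, with t = 4.303:

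- SD 0.05: 4.303 × 0.05/1.732 = 0.12
- SD 0.10: 4.303 × 0.10/1.732 = 0.25
- SD 0.15: 4.303 × 0.15/1.732 = 0.37

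Around a mean of 0.8, the two wider intervals pass the scale maximum (0.8 + 0.25 = 1.05), so they indicate the order of the uncertainty and are not literal limits. This step concerns the single-source score and does not measure the missing comparison.

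**The case against.** **The comparison may be specified elsewhere.** The article condenses a fuller protocol, its timeline and schedule figures are not available here, and the abstract's reference to the SCS presupposes values for both sources. A reader might infer from the outcome section that no MDM-C score will be collected and that the hypothesis can never be tested. The text does not support that: it is silent on collecting an MDM-C score and does not rule it out. What stands is narrower and sufficient. The article is explicit about the instrument, the object scored, the raters, the summary and the success rule, all for ADBoard alone. That conflicts with its own abstract and objective, and so is more than a detail left to an analysis plan.

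**Reaching 0.8 is not said to prove the comparison.** A reader might infer that the plan lets the trial declare objective 2 achieved on the strength of 0.8. The rule says only that this outcome is met. The defect is a mismatch between objective and endpoint, not a written licence to claim superiority.

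**Three raters are not the fault.** One might go further and call the explainability outcome uninformative because only three physicians score it. The interval widths rest on an assumed SD and on one score per physician, and the article does not say that the result is to generalise beyond these three. An interval for a descriptive target is commonly left to the analysis plan. This objection stands, and the precision figures are illustrative only.

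**The weight is modest.** This is the second of two secondary outcomes. It touches neither the kappa endpoint nor the sample size, and a change of wording would resolve it. That also stands.

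**Conclusion.** The point holds as a contradiction between objective and endpoint. The abstract and objective 2 state a comparison, with MDM-AB expected to be higher; the registration table and the outcome section define an ADBoard-only score with a pass mark of 0.8; the planned analysis does not bridge the two. As written, the outcome and its success rule do not test the hypothesis and can disagree with it in either direction.

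This conclusion rests on the text alone and needs no assumption about variability. It should be put right, but it is confined to a secondary outcome. The half-width of about 0.25 (0.12 to 0.37) for a three-rater mean depends wholly on the assumptions stated with it and adds only that the 0.8 rule is imprecise under them.

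**What to change.** Choose one of two changes before results are analysed.

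1. **Keep the comparison.** Define the SCS outcome for both sources. Have the same three specialist physicians score the MDM-C and the MDM-AB protocol of the same prespecified sample of Arm A cases, in random order. According to the data collection plan, every Arm A case is discussed at MDM-C and then processed by ADBoard, so both results exist for each case. Analyse the case-level paired difference with a 95% CI that accounts for rater and case, and fix the number of cases in advance; one overall score per physician and source would not suffice. The cost is some extra questionnaires. One limit remains: raters cannot be fully masked, because ADBoard output is recognisable by its marked automatic entries, confidence score and justification (System architecture of ADBoard).

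2. **Withdraw the comparison.** Remove the comparative hypothesis from the abstract and the objectives, and report the ADBoard score descriptively against 0.8. This costs wording only, but gives up the comparative claim.

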## Methods and analysis

### Study setting

The single-center study will be conducted at an academic hospital, Campus Virchow-Klinikum, Charité – Universitätsmedizin Berlin, Berlin, Germany.

### Recruitment

All patients enrolled in hepatobiliary MDMs with the diagnoses specified in the inclusion criteria will be invited to join the study.

### Eligibility criteria

#### Inclusion criteria

The inclusion criteria are (1) patients above 18 years of age; (2) valid informed consent; (3) patient information available in the hospital information system and Health Data Platform; (4) registration in the hepatobiliary MDM; and (5) diagnosis of any of the following: (a) HCC, mixed cell carcinoma, or fibrolamellar carcinoma; (b) perihilar cholangiocarcinoma; (c) intrahepatic cholangiocarcinoma; (d) colorectal liver metastases; or (e) gallbladder carcinoma.

#### Exclusion criteria

The exclusion criteria are as follows: (1) patient does not consent or is incapable of giving consent; (2) patient data is unavailable in the hospital information system; and (3) patient is seeking for a second opinion and is not being treated at the study institution.

### Study design

ADBoard is a monocentric, prospective, parallel randomized controlled trial with a non-inferiority design. Participants will be randomized 1:1 using the randomization module in the Research Electronic Data Capture (REDCap) software [10] into one of two groups: either (a) MDM with ADBoard (MDM-AB) or (b) conventional MDM without ADBoard (MDM-C). Figure 1 shows the timeline of the study with its primary and secondary endpoints.

The follow-up ends with the initiation of the MDM recommendation. Both study arms will be validated by an external, conventional MDM conducted at the end of the follow-up period to serve as a reference. This reference MDM will be conducted by experts in hepatobiliary tumors from the departments of surgery and oncology as soon as the recommendation has been initiated, typically within 4 weeks after conducting MDM-C and MDM-AB. It would only be conducted as part of the study. Its slightly delayed timing would ensure that any information not available at the time of the initial MDM-AB and MDM-C could be processed.

To improve adherence to the study, the research team will ensure the availability of logistics such as the designated computer enabled to run the algorithm and physician availability and presence during the MDM to carry out the intervention.

Both groups of participants would receive baseline care, that is, all cases would be evaluated at a conventional MDM. Participants retain the right to accept or refuse recommended treatments.

### Data collection plan

All participants’ cases would be discussed at MDM-C. For participants randomized to MDM-AB, these cases would be processed by the ADBoard algorithm in real-time, immediately after the MDM-C session has taken place. The outcomes of both MDM-C and MDM-AB would be recorded using secure, web-based REDCap tools hosted at Charité – Universitätsmedizin Berlin [10, 11].

### Outcomes

#### Primary outcome measures

We will study the concordance of the recommendations of MDM-C and MDM-AB. The interrater reliability of the agreement between recommendations of ADBoard and MDM-C will be measured using Cohen’s kappa value, with a target value of ≥ 0.75.

We will also assess the reproducibility of the therapy recommendations made by ADBoard. The intrarater reliability will be measured by testing all participants’ cases several times by ADBoard according to the required sample size with sufficient statistical power (test–retest). Interrater and intrarater reliability will be evaluated descriptively (percentage of agreement, contingency tables), and finally, Cohen’s kappa value will be assessed.

#### Secondary outcome measures

The first secondary outcome measure is the completeness of decision-relevant parameters. To prefill the required parameters in the online tumor protocol, ADBoard searches the health information system for each required parameter. The three possible documentation statuses are (1) “present”—search performed and data are present, (2) “detected as missing”—search performed and data are absent, and (3) “missing”—search was not performed for the required parameter. The outcome is achieved if documentation is complete, defined as documentation status “present” or “detected as missing,” in ≥ 75% of all ADBoard-assisted decisions.

The second secondary outcome measure is the explainability of ADBoard measured using the System Causability Scale (SCS) [1]. The SCS consists of 10 questions. An overall score between 0.2 (lowest quality) and 1.0 (highest quality) can be achieved. Three specialist physicians at the departments of surgery and oncology will complete it, and the mean will be calculated. Achieving a mean score of ≥ 0.8 is considered to have met this outcome.

### Participant timeline

The schedule of enrollment, interventions, and assessments is displayed below in Fig. 2.

**Fig. 2 Fig2:**
[figure not shown]
Schedule of enrollment, interventions, and assessments

### Harms

We do not foresee any potential harms or adverse effects occurring because of the study. The participants would ultimately receive the same recommendations and treatment options with or without the interventions. The recommendations made by the decision algorithm would be recorded purely for study purposes only.

### Sample size

#### Calculation of sample size

The evaluation of the primary outcome is based on Cohen’s kappa test (inter- and intrarater comparison) for nondichotomous decision-making. There are five possible recommendation categories: surgical resection or transplantation, chemo-/immunotherapy, interventional therapy, re-intervention, and further diagnosis. A five-category nominal scale will be used between different raters or different ratings of the same instance. The frequency of each category is not evenly distributed here but is estimated to be 0.3 for resection or transplantation, 0.3 for chemotherapy, 0.2 for follow-up, 0.1 for intervention, and 0.1 for further diagnosis. To capture any deviation from this estimate, different expressions of the frequencies were included in Table 1. The null hypothesis was defined as a Cohen’s kappa value of 0.7, as reliability below this value can be considered clinically unacceptable. The reliability strength to be achieved was set at 0.8 (primary endpoint: kappa value ≥ 0.75). Based on these specifications, the required numbers of cases were taken from the calculations of Bujang and Adnan [12]. A total of 3000 patients will be included in the retrospective part of the study and 1200 patients will be included in the prospective part.

**Table 1 Tab1:** Indication of the numbers of cases required for different relative frequencies of a 5-category nominal scale [12]. Number of categories: 5, type I error (*ɑ*): 0.05, null hypothesis (Cohen’s kappa): 0.7, primary endpoint (Cohen’s kappa): 0.8

Relative frequencies	Required number of cases (power 80%)	Required number of cases (power 90%)
0.3, 0.3, 0.2, 0.1, 0.1	240	311
0.3, 0.25, 0.2, 0.1, 0.05	254	329
0.6, 0.1, 0.1, 0.1, 0.1	306	400

The required numbers of cases depending on the relative frequencies of the recommendation types are displayed in Table 1.

